## **Methods**

### **Trial design**

A parallel two group randomized controlled clinical trial will be conducted to assess the use of ForeSite PT™ system on a pressure-related skin and tissue changes, with progression to pressure ulceration; interface pressure; and the perceptions of healthcare providers and patients to the ForeSite PT™ system. Eligible consenting inpatients will be randomly allocated to either have the ForeSite PT™ system and the LCD monitor turned on (intervention group), or have the ForeSite PT™ system and the LCD monitor turned off (control group) in a ratio of 1:1. Both groups will be included in the study up to a maximum of 7 days. Interface pressure and clinical outcomes will be measured at baseline (within 24 hours of admission) and on the last day of enrollment in the trial (within 24 hours prior to discharge, or on the seventh day (whichever comes first)). The perceptions of patients allocated to the intervention group, and the perceptions of healthcare providers each time a patient in their care is allocated to the intervention group, will be measured on the last day of enrollment in the trial or on the seventh day (whichever comes first).

Ethics ID number: REB13-0794

Study Title: Effectiveness of a pressure-sensing mattress system for reducing the risk of pressure ulcer formation by lowering interface pressure in vulnerable patient populations: Parallel-two-group randomized trial

PI: [name]

Version number/date: V2 01/04/2014

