### 205 **Secondary Outcomes**

Ethics ID number: REB13-0794

Study Title: Effectiveness of a pressure-sensing mattress system for reducing the risk of pressure ulcer formation  
by lowering interface pressure in vulnerable patient populations: Parallel-two-group randomized trial

PI: [name]

Version number/date: V2 01/04/2014

- 206 1. A composite of endpoints that reflect compromised skin and soft tissues, with potential for  
 207 progression to overt pressure ulceration. This will include:  
 208 a. skin discolouration;  
 209 b. localized tenderness without skin breakdown;  
 210 c. Stage I and II (partial thickness) pressure ulcer formation;  
 211 d. Stage III and IV (full thickness) pressure ulcer formation;  
 212 e. unstageable/Unclassified: Full thickness skin or tissue loss – depth unknown;  
 213 f. suspected Deep Tissue Injury – depth unknown; or  
 214 g. presence of any skin or wound infection (i.e., cellulitis, infected ulcers, or osteomyelitis).

215 This outcome will be measured by a head-to-toe skin clinical assessment for detection of pressure-  
 216 related skin changes and for overt ulceration by the Research Nurse. This assessment will be conducted  
 217 within 24 hours of admission and 24 hours prior to discharge, or on the seventh day (whichever comes  
 218 first). This information will be noted on a form, which requires the Research Nurse to circle the skin  
 219 areas where the patient may have skin changes or a pressure ulcer. They will label the circled area with  
 220 the numbers 1 to 9 that correspond to predetermined categories of pressure-related skin changes and  
 221 stages of pressure ulcer development.

222 The presence of a pressure ulcer and its severity, as well as the development of other skin condition  
 223 changes, will be determined as per the National Pressure Ulcer Advisory Panel's categories/staging  
 224 definitions (2,3,4,5,6,7) and other skin appearance changes (1,8,9) described below:

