230 These questions were utilized in a prior pilot study assessing healthcare providers' perceptions to  
231 the interface pressure information provided on the LCD monitor, and the impact of this information  
232 on patient care. The survey will be administered to each healthcare provider once after their first  
233 use of the ForeSite PT™ system in the trial by the Research Nurse or the Research Assistant on the  
234 patient's last day of enrollment or on the seventh day (whichever comes first), and will take  
235 approximately 10 minutes to complete.

236

237 3. Perceptions (both positive and negative) of patients (and if appropriate, family members) allocated  
238 to the treatment group to the ForeSite PT™ system. This outcome will be measured by a survey  
239 consisting of seven close-ended and open-ended questions about prior experience with pressure  
240 mapping technology and the ForeSite PT™ system (including sensor overlay and monitor display of  
241 their pressure distribution) on their care and comfort. The survey will be administered by the  
242 Research Nurse or the Research Assistant, and will take approximately 10 minutes to complete.

243 In addition, a pressure ulcer risk assessment will be conducted, and demographic information and  
244 information on medical history will be collected from patient charts, to establish a patient profile at  
245 baseline, within 24 hours of admission, by the Research Nurse or the Research Assistant.

246 The Braden Scale will be administered to determine the patient's level of risk at pressure ulceration. The  
247 Braden Scale was developed to assist healthcare providers with assessing a patient's level of risk for  
248 pressure ulcer development and the course of a particular treatment. It is a summated rating scale  
249 composed of six subscales: sensory perception, activity, mobility, moisture, friction, and nutrition. Each  
250 subscale is scored from 1-3 or 1-4, for a total score that ranges from 6-23. A lower total score indicates a  
251 lower level of functioning and therefore a higher level of risk for pressure ulceration. Second, a head-to-  
252 toe skin assessment will be conducted for detection of pressure-related skin changes and for overt  
253 ulceration. It requires circling skin areas where the patient may have skin changes or a pressure ulcer,  
254 and labelling the same area with the numbers 1 to 9, which correspond with stages of skin change and  

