### **Randomization**

The random allocation of patients to intervention vs. control groups will be conducted following enrollment in the trial (i.e., admission to study settings). Allocation will be completed in a concealed manner by a research methodologist in the Calgary Institute for Population and Public Health at the University of Calgary, using a random number generator that will produce a randomization list organized in blocks of 6.

The list will be used to prepare sealed, opaque, allocation envelopes that will be stored in a secure documents cabinet in the clinical setting. The Research Nurse and Research Assistant will then access these envelopes in the secure storage area to determine patient allocation at the time of randomization.

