### **Blinding**

The researchers, who will be involved in data analysis, including the Principle Investigator, Co-Investigators, and the Research Coordinator, will be blinded to treatment allocation. The Research Nurse and the Research Assistant will both be involved in participant recruitment, the randomization process, and data collection, and will not be blinded to treatment allocations. It will be impossible to blind

Ethics ID number: REB13-0794

Study Title: Effectiveness of a pressure-sensing mattress system for reducing the risk of pressure ulcer formation by lowering interface pressure in vulnerable patient populations: Parallel-two-group randomized trial

PI: [name]

Version number/date: V2 01/04/2014

289 participants and healthcare providers as they will be able to see if the LCD monitor that displays  
290 information about the patient's surface pressure on the bed is mounted to headwall.

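### Baseline skin, Braden and pressure measurements are not required before allocation is revealed, and the skin rater is unblinded at both examinations

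*Protocol*

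**What the plan says.** **Timing of baseline.** The Trial design section states: "Interface pressure and clinical outcomes will be measured at baseline (within 24 hours of admission"). The Secondary Outcomes section sets the same window for the head-to-toe skin assessment. It has the risk profile, which includes the Braden Scale, collected at "baseline, within 24 hours of admission, by the Research Nurse or the Research Assistant".

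**Timing of allocation.** The Randomization section states: "The random allocation of patients to intervention vs. control groups will be conducted following enrollment in the trial (i.e., admission to study settings"). The Research Nurse and Research Assistant use "these envelopes in the secure storage area to determine patient allocation at the time of randomization". The order of baseline and envelope opening is not given.

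**Who does what.** Under Recruitment, the Research Nurse sets up the overlay and monitor and checks them daily. Under Secondary Outcomes, the Research Nurse performs the skin assessment and repeats it with the Braden Scale at the end. The Blinding section says that the Research Nurse and Research Assistant "will both be involved in participant recruitment, the randomization process, and data collection, and will not be blinded to treatment allocations". It calls blinding impossible for participants and healthcare providers, and gives no reason for leaving the skin assessor unblinded. Those who analyse the data are to be blinded.

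**How the data are used.** The first secondary objective is the incidence of compromised skin and soft tissue. The Analysis section stratifies by Braden score and lets notable baseline imbalances trigger adjusted logistic regression. Interface pressure is sampled automatically at 1 Hz (Primary Outcome).

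**The concern.** A baseline value is protected by randomization only if it is fixed before the arm is known and before the intervention starts. Here the window is tied to admission rather than allocation, so a patient can be allocated, have the display switched on and only then be examined, all within the protocol. Three things follow.

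1. **Skin map.** Incidence is judged against the baseline record. A rater who knows the arm can, without intending to, record more early change as already present in one arm, which lowers that arm's count of new lesions. Label 1 on the form, blanchable erythema, is by the protocol's own description potentially reversible and leaves room for judgement.
2. **Braden score.** It is the stratifier and underlies the research question on higher-risk patients. Scored after allocation by someone who knows the arm, it is no longer a clean pre-randomization variable.
3. **Interface pressure.** The sensor is objective, so rater bias does not arise. If the display is already on, however, the baseline reading in the intervention arm may already reflect display-guided repositioning. Any baseline-to-end comparison then starts from a treated value.

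Separately, the final skin rating is made by the person who runs the device. That is ordinary detection bias, and correcting the baseline order alone does not remove it. Blinding the analysts cannot repair ratings made with knowledge of the arm.

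**Working it through.** **Step 1: set the sections side by side.**

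| Step | What the protocol fixes | What it leaves open |
|---|---|---|
| Consent, then device set-up by the Research Nurse (Recruitment) | Set-up is described directly after consent | No baseline step is placed between them |
| Allocation (Randomization) | After enrolment, equated with admission | Whether before or after baseline |
| Baseline skin, Braden, pressure (Trial design, Secondary Outcomes) | In the first 24 hours from admission | Whether before the envelope or display-on |
| Final skin and Braden (Secondary Outcomes) | Research Nurse, last 24 hours before discharge or day 7 | Whether the display is covered |
| Blinding | Research Nurse and Research Assistant unblinded | Why the skin rater must be |

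Baseline after allocation is therefore permitted but not prescribed. Unblinded skin rating is prescribed.

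**Step 2: reproduce the plan's figure.** Inputs from the Sample size section: 30% versus 20%, alpha 0.05 (taken as two-sided), power 80%. With pooled rate 0.25:

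n = [1.960·√(2·0.25·0.75) + 0.842·√(0.30·0.70 + 0.20·0.80)]² / 0.10² = (1.2002 + 0.5119)² / 0.01 = 293.2, rounded up to 294 per arm.

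This matches the stated 294 and is not in dispute. Power at 300 per arm is 80.9%.

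**Step 3: illustrate what arm-aware rating could do.** Assumptions that are not in the protocol: a true skin-event rate of 30% in both arms (the protocol gives 30% only for the primary outcome) and a spurious shift d in the recorded intervention-arm rate. With p₁ = 0.30, p₂ = 0.30 − d, n = 300 and p̄ their mean:

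- SE₀ = √(2p̄(1−p̄)/n)
- SE₁ = √((p₁(1−p₁) + p₂(1−p₂))/n)
- chance of p<0.05 = Φ((d − 1.96·SE₀)/SE₁) + Φ((−d − 1.96·SE₀)/SE₁)

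For d = 0.03: p̄ = 0.285, SE₀ = 0.03686, SE₁ = 0.03684. The first term is Φ(−1.147) = 0.126 and the second is 0.003, total 0.129.

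For d = 0.05: SE₀ = 0.03646, SE₁ = 0.03640. The first term is Φ(−0.590) = 0.278 and the second is below 0.001, total 0.278.

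The base rate is itself assumed, so the last column repeats the calculation from 20%.

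| Assumed spurious shift | From 30% | From 20% |
|---|---|---|
| 1 point | 6% | 6% |
| 2 points | 8% | 10% |
| 3 points | 13% | 16% |
| 5 points | 28% | 36% |

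**Step 4: tie the shift to the baseline record.** Suppose a share m of the intervention arm's new lesions is recorded as already present at baseline. The recorded rate becomes 0.30(1 − m). Shares of 5%, 10%, 15% and 20% give 28.5%, 27%, 25.5% and 24%, and chances of p<0.05 of 6.9%, 12.9%, 23.3% and 38.0%. The 3-point shift in step 3 thus equals misrecording one new lesion in ten.

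**The case against.** The strongest reply is that the order is inferred from silence. No section places baseline after allocation, the word baseline itself suggests the opposite, and the order of tasks on day one could sit in an operations manual. Part of this stands: a reader might infer that baseline always follows allocation, and the text does not say so. But the protocol does fix a time anchor, and fixes it to admission. Staff could follow it exactly and still obtain an arm-aware baseline.

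Other stronger readings also fail:

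- **That the primary outcome is rater-biased.** It is recorded by the sensor. Only the skin ratings and the Braden score depend on judgement.
- **That a treated baseline pressure absorbs the effect through adjustment.** No baseline-pressure covariate is specified. The planned comparisons are Chi-square or Fisher tests, with logistic regression only when baseline characteristics differ notably.
- **That 13% or 28% is this trial's false-positive rate.** Both the event rate and the shifts are assumed.

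It is also fair that the lack of blinding is openly stated, that labels 2 to 7 follow published staging definitions, and that localized tenderness, although in the composite, has no label of its own on the form. These points limit the room for judgement without removing it. Separating roles will not guarantee blinding either: a nurse on the unit for up to seven days may learn the arm from the monitor or from ward staff.

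**Conclusion.** The concern holds as a defect of timing and task assignment. The protocol permits the baseline skin map and Braden score to be recorded after allocation by someone who knows the arm, and permits baseline pressure to be recorded with the display on. It also assigns both skin ratings to an unblinded nurse who runs the device, without saying why the rater cannot be blinded.

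The weight falls on the skin composite and on analyses by Braden stratum. For the primary pressure outcome the issue is display exposure at baseline only. The size cannot be estimated from the document. If skin events run near 30%, shifts of 1 to 2 points do little (6% to 8%), while 3 to 5 points raise the chance of a false positive to about 13% to 28%. A lower base rate makes the same absolute shift more damaging. The point should be acted on before recruitment, because ratings made with knowledge of the arm cannot be corrected at analysis.

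**What to change.** **Sequence.** Amend Trial design, Secondary Outcomes and Randomization so that, for every patient, the skin map, the Braden score and a short pressure recording with the display off are completed and recorded before the envelope is opened. The overlay goes in place with the display off in both arms. The 24-hour window can stay as an outer limit.

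**Roles.** Where the two existing roles allow, have the Research Assistant open envelopes, handle the display, make the device checks and administer the surveys, since surveys confined to the intervention arm reveal allocation. The Research Nurse then rates skin with the display off or covered in both arms. Amend Recruitment and Blinding to match, and state there that this reduces unblinding of the assessor without guaranteeing blindness.

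**Cost.** A short delay before the display is switched on in the intervention arm, one brief added recording, and some reassignment of tasks between existing staff. The system already samples silently with the display off in the control arm, so no new equipment is implied. The sample size is unchanged.

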## **Participants**

### ***Recruitment***

Identification of eligible inpatients will be facilitated by the charge nurse, the patient care manager, and nurses on their respective units, and by daily review of new admissions. After an eligible patient has been identified, the Research Nurse or the Research Assistant will ask him or her (or a substitute decision-maker, if not capable of consenting), if he or she would be interested in participating in a study to evaluate a pressure sensing technology that provides real-time feedback to healthcare providers. If the patient agrees to participate, he or she will be asked to provide informed consent. The Research Nurse will set up the ForeSite PT™ system, including placing the sensor overlay under the linen and mounting the LCD monitor to the headwall. The Research Nurse will ensure that the overlay and monitor are functioning properly on a daily basis, and will instruct housekeeping on sterilization practices of these device components.

### ***Eligibility***

The selection of participants will be based on the following inclusion and exclusion criteria:

Inclusion criteria:

- Adult, man or woman, with a minimum age limit of 18 years old;
- Expected to have a length of stay on the unit of at least 4 days;
- Require assistance with bed mobility or completely dependent for bed mobility (identified as those who had difficulty shifting themselves independently and who needed assistance with turning within their bed and/or getting in and out of bed);
- Cognitively competent to provide consent, or is cognitively impaired and have a family member provide consent on their behalf; and
- Not near the end of life within three days of enrollment in the study.

Exclusion criteria:

- Have a planned admission to another unit (including those identified as a setting for data collection in the study) within three days of enrollment in the study;
- Sleep in a chair at night; and
- Whose clinical care would be negatively impacted if turned or repositioned.

### ***Setting***

This trial will take place at five inpatient care settings at the Foothills Medical Centre, a tertiary care institution, in Calgary, Alberta, Canada. The three inpatient care settings include: 1) Units 36 and 37 in the Special Services Building, the internal medicine services that cares for vulnerable medical inpatients with immobility arising from complex multi-system medical illness; 2) the intensive care unit (ICU) that

Ethics ID number: REB13-0794

Study Title: Effectiveness of a pressure-sensing mattress system for reducing the risk of pressure ulcer formation by lowering interface pressure in vulnerable patient populations: Parallel-two-group randomized trial

PI: [name]

Version number/date: V2 01/04/2014

175 cares for sedated and immobilized patients requiring life support for prolonged periods of time; and 3)  
176 Unit 112 and Unit 58, the neurological rehabilitation unit that cares for patients with prolonged  
177 immobility and vulnerability resulting from spinal cord and/or significant head injuries.

## 178 **Intervention**

179 All eligible consenting inpatients will receive usual care by their healthcare providers, and undergo  
180 interface pressure monitoring by the ForeSite PT™ system.

## 181 **Treatment Group**

182 Inpatients allocated to the treatment group will have the ForeSite PT™ system's LCD monitor turned on  
183 (i.e., real-time images of interface pressure will be displayed on the monitor) during their enrollment in  
184 the trial.

## 185 **Control Group**

186 Inpatients allocated to the control group will have the ForeSite PT™ system's LCD monitor turned off and  
187 hidden (i.e., real-time images of interface pressure will not be displayed on the monitor). As the ForeSite  
188 PT™ system will continue to sample interface pressure with the display turned off, this enables patients  
189 enrolled in the control group to undergo silent monitoring.

## 190 **Outcomes**

### 191 **Primary Outcome**

- 192 1. A composite of interface pressure measurements that reflect the distribution of interface pressure  
193 at predetermined time intervals. These measures include:
- 194 a. proportion of participants that have pressure readings greater than 40 mmHg;
  - 195 b. average interface pressure (excluding sensels with 0mmHg reading); and
  - 196 c. the absolute number of sensels with pressure readings greater than 40 mmHg.

197 The measurement of this outcome will be facilitated by the ForeSite PT™ system's sensor overlay that  
198 continuously collects pressure readings. The array of the sensor overlay is a capacitive sensor with a  
199 0.625" spatial resolution. There are 52 rows x 118 columns for 6,136 sensing points. The ForeSite PT™  
200 system's software continuously samples interface pressure at a rate of 1 Hz, which can then be  
201 extracted for analysis. The data file is in a proprietary binary format, and can be exported to TXT or CSV  
202 formats for import into a spreadsheet program for analysis. This will be achieved by the sampling of  
203 pressure readings at specified time intervals before and after turning/repositioning when the ForeSite  
204 PT™ system's LCD monitor is turned on, and when it is turned off.

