Study Title: Effectiveness of a pressure-sensing mattress system for reducing the risk of pressure ulcer formation by lowering interface pressure in vulnerable patient populations: Parallel-two-group randomized trial

PI: [name]

Version number/date: V2 01/04/2014

component of prevention and treatment protocols. The best practices pertaining to a specific turning regiment varies from the National Pressure Ulcer Advisory Panel (NPUAP) recommending repositioning every two hours and the European Pressure Ulcer Advisory Panel (EPUAP) recommending every four hours. Thus pressure ulcer prevention and management are necessarily labour-intensive.

Continuous pressure imaging (or interface pressure mapping) of the interface pressure between the body and support surface could be an effective technology as part of an overall strategy for the prevention and management of ulcers. By placing a thin mattress or sensor pad with monitoring capabilities under a patient, pressure imaging interprets the interface pressures and provides the patient's real-time pressure points on a corresponding computer screen, which can assist healthcare providers determine when a patient should be re-positioned (Hanson). XSENSOR Technology Corporation designed the ForeSite PT™ Patient Turn System (here in "ForeSite PT™ system"), which can continuously monitor bed surface interface pressure and track the patient's exposure to that pressure. The ForeSite PT™ system provides patient turn tracking to assist with management of the patient turn schedule. The pressure exposure monitor provides a visual image that quantifies historical pressure information. The exposure monitor assists clinical staff by alerting them to the location of body areas that have experienced the greatest exposure to pressure. The surface pressure monitor provides clinical staff with a visual image of the pressure distribution across a patient's body. It can be used by care providers to identify high pressure areas in real time and to validate that patient repositioning has successfully relieved pressure.

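### Primary pressure readings are tied to turning events, whose timing and number the display is meant to change; short or fixed windows around turns can miss shorter high-pressure dwell and give unequal chances of a reading above 40 mmHg

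*Protocol*

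**What the plan says.** The protocol describes when interface pressure is read in three places.

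- Primary Outcome, opening sentence: the composite reflects the pressure distribution "at predetermined time intervals. These measures include" three components, namely the proportion of participants with readings above 40 mmHg, the average pressure, and the number of sensels above 40 mmHg.
- Primary Outcome, last sentence: sampling is of "pressure readings at specified time intervals before and after turning/repositioning when the ForeSite" monitor is on, and when it is off.
- Trial design: "Interface pressure and clinical outcomes will be measured at baseline (within 24 hours of admission) and on the last day of enrollment in the trial".

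On what the device does, the Background says pressure imaging gives a real-time picture "which can assist healthcare providers determine when a patient should be re-positioned", and that the "system provides patient turn tracking to assist with management of the patient turn schedule". Research question 1 under Objectives makes turning and repositioning the route by which pressure is to fall.

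On what is recorded, the "system's software continuously samples interface pressure at a rate of 1 Hz, which can then be" extracted. Under Control Group, the hidden display still allows patients "enrolled in the control group to undergo silent monitoring". Continuous data therefore exist in both arms.

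The protocol does not give the interval lengths, the number of turns sampled per patient, or any weighting by time.

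**The concern.** A turn is a post-randomisation event, and changing when and how often it occurs is part of what the display is for. If readings are taken around turns, treatment influences when and how often the primary outcome is observed. Two consequences follow when the windows are short or contain a fixed number of readings.

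1. **Dwell time drops out.** A high-pressure position held for four hours supplies the same readings as one ended after ninety minutes. Ending such positions sooner is one of the ways the device should work, and the comparison would hardly show it.
2. **Opportunity differs by arm.** If every turn is sampled, the arm that turns more has more chances to record a value above 40 mmHg. Component (a) could then look worse in that arm with no rise in exposure.

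Separately, the three timing descriptions can select different data from the same continuous recording, so the primary result may depend on which one the analyst follows.

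**Working it through.** **The plan's own figure.** With 30% against 20%, two-sided alpha 0.05 and 80% power:

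n = [1.960·√(2·0.25·0.75) + 0.842·√(0.3·0.7 + 0.2·0.8)]² / 0.10² = 293.2, so 294 per arm.

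This matches the protocol. Power at 300 per arm is 80.9%. The sample size is not in dispute.

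Everything below is illustrative, because the protocol supplies none of the inputs.

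**A. Dwell time.** Assumptions: position pressures have mean 28 and SD 6 mmHg in both arms. Control positions last 4 h. Intervention positions last 1.5 h if above the mean and 3 h if below. The window is 72 h.

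- Mean of the upper and lower halves: 28 ± 6·√(2/π) = 28 ± 4.79, that is 32.79 and 23.21.
- Clock-time mean, intervention: (1.5·32.79 + 3·23.21)/4.5 = 26.4. Control: 28.0. Difference -1.6 mmHg.
- One reading per position: (32.79 + 23.21)/2 = 28.0 in both arms. Difference 0.
- Positions held: 72/2.25 = 32 against 72/4 = 18.

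Simulation with random dwell times agrees: about -1.6 by clock time, within 0.1 of zero when turn-anchored, and 33 against 19 turns.

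**B. Chance of a reading above 40 mmHg, same model.** P(position > 40) = P(Z > 2) = 0.02275. Take component (a) as any sampled reading above 40.

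- Control: 1 - 0.97725^18 = 34%.
- Intervention: 1 - 0.97725^32 = 52%.
- Share of time above 40: 2.3% in control, 2.3%·1.5/2.25 = 1.5% in intervention.

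Exposure falls by a third while the participant-level proportion rises.

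**C. The planned 30% to 20% effect.** Assume independent windows and the any-reading rule. With r times as many turns, the intervention rate becomes 1 - 0.8^r.

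| r | Observed rate | Power, 300 per arm |
|---|---|---|
| 1 | 20% | 81% |
| 1.25 | 24.3% | 34% |
| 1.5 | 28.4% | about 6% |
| 2 | 36% | reversed |

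A ratio of 2 is the span between the 2 h and 4 h guideline intervals in the Background. Those are not expected rates for the arms.

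**D. Where the effect is not lost.**

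- Sample every 30 min for up to 3 h before each turn, stopping at the previous turn. In model A the upper and lower intervention positions give 3 and 6 readings, so the mean is (3·32.79 + 6·23.21)/9 = 26.4 and the -1.6 returns. With random dwell times the difference is about -1.5 to -1.6.
- If the display improves the chosen positions by 1, 2 or 3 mmHg, one-reading-per-turn sampling shows -1, -2 or -3.
- The pre-turn difference in model A is about 0.0.

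**The case against.** The strongest reply has four parts.

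**The near-zero result in model A is built in.** Both arms draw positions from the same distribution, so only dwell time can differ. The protocol's route is wider: research question 1 concerns the method of repositioning, and the Background says the monitor can confirm that a turn has relieved pressure. Readings before and after a turn measure that directly. This stands, so turn-anchored sampling can miss part of the effect but does not miss all of it.

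**Interval lengths, turns sampled and weighting belong in an analysis plan, which is not shown.** This stands in part. Long pre-turn windows recover the dwell effect, and a fixed number of turns per patient would equalise opportunity. It is therefore not true that every turn-anchored rule fails. But the protocol itself names the turn as the anchor, and nothing in it secures a rule that avoids the problem.

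**The three timings can be nested:** days under Trial design, a general statement, then its detail. That is possible, and the last sentence of Primary Outcome follows sentences on data export, so its reference is unclear. The wording is unreconciled; it does not prove three rival rules.

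**A reader might infer that staff turn patients when pressure is high, so pre-turn readings in the intervention arm are selected for high values.** The documents do not show this, and model A does not produce it: when every turn is sampled, each position enters once and the pre-turn difference is about zero.

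**Conclusion.** The point holds in a limited form. The primary outcome is tied to a post-randomisation event that the display is designed to change. With short or fixed windows around each turn, the comparison is insensitive to shorter time at high pressure, and it can give the more frequently turned arm more chances of exceeding 40 mmHg. It remains sensitive to better positioning.

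Size and direction cannot be computed from the protocol. The -1.6 against 0 mmHg, the 34% against 52%, and the fall in power from 81% to 34% or 6% rest on assumed dwell times, pressure spread, turn ratios, independent windows and an any-reading rule. They show what could happen, not what to expect. A reader might infer that the trial is certain to be biased, or biased in a known direction; the documents support neither.

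The need to reconcile the timing wording in Trial design and Primary Outcome does not depend on any simulation.

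**What to change.** Define the primary pressure measures on a schedule independent of turning. For every patient in both arms, use all 1 Hz frames, or one frame per fixed clock interval, from allocation over one common window that the sponsor states. Summarise them as a time-weighted value per patient, for example mean pressure and the share of time or of sensels above 40 mmHg. Keep the readings before and after turns as a secondary measure of repositioning quality, with the intervals and the number of turns sampled stated. Align Trial design with Primary Outcome so that one timing rule remains for the primary measures.

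The cost is small: the recordings are already planned in both arms, so no new measurement is needed. It takes extra data processing and a restated endpoint definition. Because 294 per arm rests on a binary event of 30% against 20%, the sample size paragraph should say which restated measure that event refers to.
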